
#### Sensitivity Analyses

To assess potential uncontrolled confounding of the results, sensitivity analyses will be conducted by excluding separately and concurrently the participants most likely to influence the effects of the 3 types of care settings: (1) ≥65 years; (2) with ≥1 comorbidity; (3) with either asthma or COPD; (4) with ≥1 regular medication; (5) with any abnormal vital signs; (6) in the lowest and highest quartile of the deprivation index; and (7) smokers. The analyses will be repeated using PMEWS instead of vital signs as a marker of illness severity. To control for a potential Hawthorne effect, the analyses will be repeated, with the first 3 months of recruitment excluded to focus on the data collected after the providers have become used to being observed.

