#### Statistical Analysis

All main analyses will be conducted primarily on participants assessed in person in any of the care settings. Participants assessed by telemedicine will be analyzed and compared separately between sites where it is implemented. The value delivered at each participating site and on average in each care setting type will be illustrated with an operational effectiveness graphic [114]. Adjusted costs of care for acute ambulatory respiratory conditions will be plotted on the x-axis and adjusted return visits within 72 hours on the y-axis. Points closest to 0 on both axes represent the highest value of care (Multimedia Appendix 6). Indeed, the lower the return visit proportion and cost of care, the higher the value of care. Similar graphics will be used for patient-centered outcome measures. To compare EDs, walk-in clinics, and primary care physician practices, multilevel generalized linear models will be used with probability distributions adapted to the outcome under evaluation. To adjust for confounding (differences in case mix between care settings), an overlap weights approach [115,116] will be used, wherein each individual receives a weight factor that is proportional to the inverse of the probability of choosing a particular setting. Subjects that differ fundamentally between settings are attributed a weight of 0 and are thus excluded. This approach is of the greatest interest when groups are initially very different [116]. Intuitively, overlap weights create a pseudopopulation for which treatment is independent of measured confounders, thus mimicking a randomized trial of those confounders. Overlap weights have been shown to be more robust than conventional inverse probability weighting and matching based on propensity scores [115]. The weights will be estimated using a multinomial logistic regression model in which the dependent variable is the chosen care setting and independent variables are potential confounders or risk factors [117] for the outcomes identified in the literature: age [118,119], sex and gender [118,120], ethnicity [118,121-123], registration with a family physician [20,124], comorbidities (the Charlson index; number of regular medications) [118,125,126], asthma, FEV_1_ among patients with asthma, the Canadian deprivation index [127-129], patient perception of illness severity [130], and vital signs [131-135] as proxies for severity. The same independent variables will be used to adjust for differences in case mix between settings in the telemedicine cohort, excluding vital signs and FEV_1_. Multiple imputation will be considered as a possible means to adjust for these variables in this cohort. Overlap weights will be calculated using the values predicted by this model. We shall verify that the care setting groups are comparable according to the measured confounders after weighting by computing standardized mean differences. Differences below 10% will be considered to indicate good balance [117]. If residual imbalances are present, the weighting model will be revised. Once an appropriate balance is achieved, separate models for each outcome will be fitted to the weighted data, for which the care setting will be the only independent variable. The robustness of results with respect to unmeasured confounding will be assessed using the E-value [136,137]. Clustering by setting (eg, province, practice unit) will be taken into account using multilevel modeling (random intercept on province and practice unit). Reported cost estimates will be calculated with item-specific standardized costs (eg, Québec and Ontario average nurse unit cost). Patients referred to the ED from a participating outpatient facility but discharged home after ED assessment will be analyzed in the care setting group where they first presented, and the ED referral will be considered as a return visit. The costs of any return visits and admissions up to 7 days after the initial visit will be estimated separately and attributed to the care setting where the initial visit took place. Results of the 3 questionnaires from the patient perspective will be reported as proportions (PREM), mean costs (CoPaQ), and median scores (PROM-ED) and adjusted using the overlap weights approach. As patients seek care for symptoms, subanalysis based on presenting complaints instead of discharge diagnosis will be conducted to provide meaningful patient-oriented results. Other subanalyses will evaluate which patient profile (eg, gender [120], motivation for choosing a facility), and institutional characteristics (eg, access to x-ray) predict high quality and low costs, keeping in mind that our value assessment might not yield similar results for all subgroups or even within a group of patients with the same diagnosis. Statistical differences will be assessed with a significance threshold set at .05.

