### Challenges and Mitigation Strategies

First, as patients choose their facility, those presenting at the 3 types of setting will likely represent different populations. However, we believe that the potential confounding bias due to self-selection of the care setting can be overcome using the overlap weights approach. Extensive testing of the robustness of our findings by sensitivity analyses should allow us to avoid reaching false conclusions under the influence of uncontrolled confounding. Second, the Québec and Ontario health systems might differ enough to yield results that will not be easy to generalize. When applicable, the sources of heterogeneity will be investigated. However, Canadian provincial health care systems have fundamental similarities that reduce the risk of poor generalizability. All are based on universal coverage; all suffer from a lack of integration between primary and urgent care resources [138,139]; institutions follow the recommendations of the same accreditation organizations; and care providers are trained according to the same standards and guidelines. Third, because of the pandemic, many outpatient clinics have ceased their activities or shifted to telemedicine. Our research plan already includes participants evaluated by telemedicine and will adapt easily to any increase in this practice. If the pandemic is still ongoing in November 2021 when phase 1 is launched, we will be able to collect financial data from participating institutions, which can be done remotely. Time measurement of care processes can be postponed until phase 2 in 2023, during which the recruitment of participants is planned. Finally, if the pandemic is still a factor in 2023, we will select clinics that continue to assess patients with acute respiratory disorders.

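### The planned exclusions mostly re-test covariates already in the weighting model, so stable results say little about confounders outside that list and the protection claimed from them should be narrowed

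*Protocol article*

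**What the plan says.** The Sensitivity Analyses section states the purpose and the method together: "To assess potential uncontrolled confounding of the results, sensitivity analyses will be conducted by excluding separately and concurrently the participants" thought most able to shift the setting effects. The groups are "1) ≥65 years; (2) with ≥1 comorbidity; (3) with either asthma or COPD; (4) with ≥1 regular medication" and "5) with any abnormal vital signs; (6) in the lowest and highest quartile of the deprivation index; and (7) smokers". The section also repeats the analyses with PMEWS in place of vital signs.

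The Statistical Analysis section builds the overlap weights from a multinomial model. Its covariates include age, "comorbidities (the Charlson index; number of regular medications"), asthma, FEV1 in patients with asthma, and "the Canadian deprivation index [127-129], patient perception of illness severity [130], and vital signs [131-135] as proxies for severity". Smoking is not listed and COPD is not named separately. The same section assigns robustness to unmeasured confounding to the E-value.

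Under Challenges and Mitigation Strategies, self-selection of the care setting is the first challenge. The answer given is the overlap weights, followed by this sentence: "Extensive testing of the robustness of our findings by sensitivity analyses should allow us to avoid reaching false conclusions under the influence of uncontrolled confounding".

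**The concern.** Patients choose their setting, so the main threat is a factor that drives both that choice and the outcome and is not in the weights. Restricting the cohort on variables that the weights already balance leaves such a factor in place. The setting estimate would then look stable whether or not it is biased.

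What is at stake is how the results are read. The article attaches a conclusion (protection against uncontrolled confounding) to a set of analyses that can support only part of it. A confounded difference between emergency departments, walk-in clinics and primary care practices could pass every exclusion and be taken as robust.

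**Working it through.** **Step 1. Exclusion variables against weighting covariates** (Sensitivity Analyses against Statistical Analysis):

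| Exclusion | In the weighting model? |
|---|---|
| Age 65 or over | Yes (age) |
| At least one comorbidity | Yes (Charlson index) |
| Asthma or COPD | Partly (asthma, and FEV1 in asthma; COPD not named) |
| At least one regular medication | Yes (number of medications) |
| Abnormal vital signs | Yes (vital signs) |
| Lowest and highest deprivation quartile | Yes (deprivation index) |
| Smokers | No |

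Count: 5 fully in, 1 partly in, 1 absent; 5 + 1 + 1 = 7.

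**Step 2. What a simulation shows.** The plan gives no figure to reproduce, so every coefficient here is an assumption.

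- Size: 1,000,000 patients per scenario in three settings.
- Weights: for a patient in setting a, w = h / e_a with h = 1 / Σ(1/e_k), where e_k is the fitted probability of setting k. They were re-estimated in each restricted sample.
- Prevalences: age 65 or over 20%, abnormal vital signs 25%, asthma 12%, smoking 20%, deprivation in four equal groups. Asthma alone stands for the asthma/COPD exclusion.
- Confounder: log-odds 0.9 on choosing the emergency department and 0.9 on the return visit.
- Risk: about 5.5% without confounding, which lies within the 5% vs 10% used in the Sample Size section.

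Odds ratios, emergency department against primary care:

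| Scenario | All patients | Single exclusions | All exclusions together |
|---|---|---|---|
| No confounding | 1.00 | 0.98 to 1.00 | 0.94 |
| Unmeasured, independent of the listed variables | 1.18 | 1.18 to 1.19 | 1.17 |
| Unmeasured, correlated with age, comorbidity and vital signs | 1.17 | 1.16 to 1.18 | 1.19 |
| Smoking as the unmodelled confounder | 1.17 | smokers out: 1.00; others 1.17 to 1.18 | 1.01 |
| Severity within abnormal vital signs, model holds only normal/abnormal | 1.35 | abnormal vital signs out: 0.99; others 1.36 to 1.41 | 0.97 |
| Effect confined to abnormal vital signs, no confounding | 1.37 | abnormal vital signs out: 1.00; others 1.38 to 1.39 | 1.04 |

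The true odds ratio is 1.0 in the first five rows. In the last row there is a real effect in patients with abnormal vital signs only. The combined exclusion keeps about 12% of patients, and the 0.94 in the first row shows how much simulation noise to allow in that column.

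Rows 2 and 3: the bias survives every exclusion almost unchanged. Row 4: the smoker exclusion works. Rows 5 and 6: the exclusion moves the estimate by nearly the same amount (1.35 to 0.99, and 1.37 to 1.00), so a shift does not say whether confounding or heterogeneity caused it.

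**Step 3. A second simulation at study scale.** This used 300 cohorts of 3000, no setting effect, and an unmeasured confounder independent of the measured covariates, with log-odds per SD of 0.5 on setting and 0.6 on return visit. The spurious difference was +1.8 points in the full cohort, +1.6 after dropping the top 20% on one covariate, and +1.4 after a joint restriction keeping 24%. Part of that fall reflects the lower baseline risk of those retained. Without the confounder all three were 0.0.

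**Step 4. Why the E-value needs a yardstick.** In row 2 the weighted risks were 8.23% and 7.05%, so RR = 8.23/7.05 = 1.167. The E-value is RR + √(RR × (RR − 1)) = 1.167 + √(1.167 × 0.167) = 1.167 + 0.441 ≈ 1.61. Whether 1.61 is reassuring depends on how strongly the measured confounders act.

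**The case against.** The strongest reply is that uncontrolled does not mean unmeasured. Confounding can remain on a measured variable when adjustment is coarse, and restriction is a fair check for that; row 5 shows it working. A reader might infer that the exclusions test nothing but effect heterogeneity. The documents do not support that.

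A reader might also infer that the plan has no defence against unmeasured confounding. It does: the E-value is assigned to it. The smoker exclusion also reaches a variable outside the model, and PMEWS scores social situation and functional status, which the weighting model does not list.

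The Discussion sentence speaks of sensitivity analyses generally and may be meant to include the E-value. The simulations rest on chosen coefficients, and in two of the scenarios reported here the confounder is independent of every covariate by construction.

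Most of this stands, and it limits the point. It does not remove it. The exclusions are presented as assessing uncontrolled confounding without qualification, the Discussion never mentions the E-value, and nothing tells the reader that stable exclusions carry little information about factors outside the list.

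**Conclusion.** The point holds as one about stated purpose and interpretation. Six of the seven exclusions act wholly or partly on variables already in the weights. They can reveal residual confounding within listed covariates or effect heterogeneity, without separating them; the seventh can reveal confounding by smoking. Under the assumed coefficients, bias from a confounder outside the list persisted at odds ratios of 1.16 to 1.19 throughout, against a truth of 1.0. Those figures illustrate the mechanism and do not predict bias in this study. Nor is stability a general law, as the smoking and vital-signs rows show.

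One further inference should not be drawn: that dropping the extreme deprivation quartiles must discard half the cohort. That is so only if quartiles are cut within the cohort, which the article does not say.

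The primary estimates are unaffected. What changes is how much may be concluded from stable sensitivity results.

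**What to change.** 1. In Sensitivity Analyses, describe the exclusions as checks of residual confounding within the listed covariates and of effect heterogeneity. State that stability is not evidence against confounders outside the list. Reword the Discussion sentence so that unmeasured confounding is referred to the E-value.
2. Add smoking to the weighting model, at least as a sensitivity analysis, instead of only excluding smokers. The planned exclusion already requires smoking status.
3. Benchmark the E-value: re-estimate the weights leaving out each measured confounder group in turn and report how far the setting effect moves. Readers can then judge whether an unmeasured factor as strong as the strongest measured group would remove the result.

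Optional: repeat the analysis in patients who chose their setting for accessibility or convenience. Motivation is already recorded at the initial visit, and a subanalysis by motivation is already planned.

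Cost: wording changes and a few re-runs of the weighting model, with no data beyond what the plan already needs. The stated protection against confounding becomes more modest.

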#### Recruitment Procedures on the Initial Visit

A research nurse in collaboration with local clerks at each site will screen eligible patients after on-site registration or web-based scheduling, but before assessment by a physician, based on presenting complaints suggestive of acute respiratory conditions. After assessment and once a targeted diagnosis is confirmed, the same research nurse will prospectively (1) obtain consent from patients; (2) ensure that the discharge diagnosis, comorbidities, and disposition plans are fully documented; and (3) administer a questionnaire to assess patient experience of care and motivation for choosing one care setting over the other. Motivation will be classified into the 6 domains of the Conceptual Model of Emergency Department Use [35]. Participants will be asked to specify whether their choice of care setting was based on accessibility, convenience, their perception of the severity of illness, their beliefs and knowledge regarding these care settings, referral and advice from a care professional or an acquaintance, or costs. They will also be requested to rate their perception of illness severity. For on-site participants only, the research nurse will also (1) assess the severity using the Pandemic Medical Early Warning Score (PMEWS), a validated severity score allowing points for age, vital signs, comorbidity, social situation, and functional status [87], and (2) perform spirometry (measured parameter: forced expiratory volume in the first second [FEV_1_]) on patients with acute asthma. A random sampling recruitment schedule will be planned to ensure a proportional representation of the hours of operation for each recruiting site. Participating EDs will recruit on a schedule similar to their paired participating clinics to include participants who could have consulted in an alternative setting and exclude night patients who differ significantly from patients seeking care during the day [88]. Recruitment will occur over a full year to encompass seasonal variability in the incidence of respiratory diseases.

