#### Sample Size

As our main analyses focus on patients assessed in person, our sample size calculation is based solely on their numbers. We estimate that the rate of return visit for ambulatory emergency conditions varies from 1% to 13% depending on the care setting [17,110,111]. To account for the potential similarity in outcomes among individuals in each of the 15 clusters, we assumed a realistic intracluster correlation of =0.02 based on previous studies and applied a correction to inflate our sample size calculation [112,113]. Using data from Campbell et al [28], at least 1485 patients (approximately 99 per cluster) will be needed to reveal a 5% difference in the proportion of return visits within 72 hours (eg, 5% vs 10%), assuming a 20% loss to follow-up and at least 30 participants per condition, based on multivariate logistic regression power analysis, type I error (α) at .05, and power at 80% (1−β). Assuming 240 recruitment days over a year at each site and the recruitment of at least 1 to 2 patients per day, our final cohort should include over 4000 patients and reach the minimal sample size in both participating provinces, which will allow for more robust comparisons and analyses.

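### Dropping the first 3 months of a single recruitment year also drops a season, so the Hawthorne check cannot by itself attribute a shift, or no shift, to observation

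*Protocol article*

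**What the plan says.** The Sensitivity Analyses section gives the check and its aim: "To control for a potential Hawthorne effect, the analyses will be repeated, with the first 3 months of recruitment excluded", in order "to focus on the data collected after the providers have become used to being observed".

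The section on recruitment at the initial visit fixes the length of accrual and the reason for it: "Recruitment will occur over a full year to encompass seasonal variability in the incidence of respiratory diseases". The Sample Size section agrees, planning on 240 recruitment days per site within one year. No second year is described.

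The Statistical Analysis section lists the variables of the weighting model: age, sex and gender, ethnicity, registration with a family physician, comorbidities, asthma, FEV1 in asthma, deprivation, perceived severity and vital signs. Calendar month, season and discharge diagnosis are not among them (asthma apart). The outcome models are then fitted to the weighted data with a single regressor, as models "for which the care setting will be the only independent variable", plus random intercepts for province and practice unit. The same section cautions that "our value assessment might not yield similar results for all subgroups or even within a group of patients with the same diagnosis".

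The Outcome Measures section stratifies in-person results by discharge diagnosis and by province. Presenting complaints and discharge diagnoses are both on the data collection list.

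**The concern.** The year of recruitment exists so that the estimate averages over the seasonal cycle of respiratory disease. The Hawthorne check removes the first quarter of that cycle. With one year per site and a common start, the patients seen while providers were new to observation are also the patients of one particular season. The 12-month and 9-month runs therefore differ in two respects, time under observation and seasonal case mix, and no term in the stated models separates them. Overlap weighting balances the settings within each run. It does not make the two runs describe the same population.

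What is at stake is how the check is read. A shift could come from the missing season. A stable result could hide an observation effect that a seasonal change in mix happens to offset. The check is stated as a way to control for a Hawthorne effect, and the bare exclusion cannot support that unaided.

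**Working it through.** The protocol gives no figure for this analysis, so there is none to reproduce. The check has two parts: what is removed, and whether season alone could move the contrast.

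**What is removed.**
- Calendar time: 3/12 = 25%.
- Recruitment days per site: 240 × 0.25 = 60, leaving 180.
- With even accrual, the stated minimum of 1485 patients becomes 1485 × 0.75 ≈ 1114.

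**Seasonal composition.** Take December to February as winter, which is 3/12 = 25% of the full year. The winter share of months 4 to 12 depends on the start month, which is not given:

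| Start month | Winter months left | Share of 9 months |
|---|---|---|
| December | 0 | 0% |
| November or January | 1 | 11% |
| October or February | 2 | 22% |
| March to September | 3 | 33% |

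**Effect on the contrast with no Hawthorne effect.** Let w be the winter share of patients. Pooled difference = w × d(winter) + (1 − w) × d(other). *Assumed* values: a between-setting difference in return visits of 8 points in winter and 4 points otherwise.

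Even accrual:
- Full year: 0.25 × 8 + 0.75 × 4 = 5.0.
- December start: 4.0, shift −1.0.
- November or January start: (1/9) × 8 + (8/9) × 4 = 4.4, shift −0.6.
- October or February start: (2/9) × 8 + (7/9) × 4 = 4.9, shift −0.1.
- March to September start: (3/9) × 8 + (6/9) × 4 = 5.3, shift +0.3.

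If winter held 40% of patients (*assumed*):
- Full year: 0.40 × 8 + 0.60 × 4 = 5.6.
- December start: 4.0, shift −1.6.
- Start that drops a third of the non-winter volume: w = 0.40/(0.40 + 0.60 × 2/3) = 0.50, giving 6.0, shift +0.4.

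If d(winter) = d(other), every shift is zero whatever the start month. The mechanism needs the setting effect to vary with season or with the mix that season brings.

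**Comparison with sampling noise.** Use 5% versus 10%, 20% loss, and no clustering or weighting. The 9-month sample is nested in the full sample, so the variance of the change is (0.05 × 0.95 + 0.10 × 0.90) × (1/n₉ − 1/n₁₂), with n per setting.
- 1485 patients: n₁₂ = 396, n₉ = 297, SE = √(0.1375 × 0.000842) ≈ 1.1 points.
- 4000 patients: n₁₂ ≈ 1067, n₉ = 800, SE ≈ 0.7 points.

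The even-accrual shifts of 0.1 to 1.0 point run from well inside one SE to about 1 to 1.5 SE.

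**Would comparing quarters identify the cause?** Take the December start with even accrual and no Hawthorne effect. Omitting quarter 1 moves the contrast from 5.0 to 4.0, a shift of 1.0. Omitting any other quarter moves it from 5.0 to 5.33, a shift of 0.33. A rule that a larger first-quarter shift signals a Hawthorne effect would here point to one that does not exist.

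**The case against.** The defence has real force on several points.

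- **Concurrent recruitment.** Each ED is paired with nearby clinics and "Participating EDs will recruit on a schedule similar to their paired participating clinics". That sentence concerns hours of operation, but if all three settings also recruit through the same months, season touches them alike and the contrast moves only through a setting-by-season interaction. This stands. It narrows the problem without removing it.
- **Heterogeneity is not established.** A reader might infer that the protocol expects the setting effect to differ by condition. It does not say so. The Statistical Analysis section says only that results might differ across subgroups, and the Discussion says that needs and preferences likely differ between conditions, which is not a statement about return visits.
- **Complete confounding is not shown.** A reader might infer it from the single year. Staggered site starts, with the 3 months counted per site, would weaken the overlap. None are described, but the Gantt diagram is not shown.
- **No interpretive rule is stated.** The section describes a restriction of the data. It does not test or estimate a Hawthorne effect, so the plan cannot be said to commit to misreading a shift.
- **Stratification exists.** If the repeated analyses include the strata by discharge diagnosis, those comparisons are largely free of shifts in condition mix, though with few patients per stratum. The protocol does not say whether they are included.

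What survives is limited but firm: in the pooled comparison as described, nothing makes the two runs target the same seasonal case mix, so the exclusion alone cannot show what caused a change or its absence.

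**Conclusion.** The point holds as a limit on what one sensitivity analysis can show. With a single recruitment year and no described staggering, early observation and calendar season overlap. Attribution to observation alone then fails if the between-setting contrast varies with season or condition mix, a possibility that the protocol leaves open.

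The size is not known. The shifts of 0.1 to 1.0 point under even accrual, and up to 1.6 points with 40% of patients in winter, rest entirely on assumed effects and volumes; for 7 of the 12 start months the even-accrual shift is only 0.3 points. They show that season can move the result, not that it will.

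A reader might go further and conclude that the check will mislead on the primary outcomes, or that the main result is biased. The documents support neither. The full-year primary estimate is unaffected, and so is the sample size. This is a minor improvement.

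**What to change.** In the Sensitivity Analyses section:

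1. Keep the 3-month exclusion, but standardise months 4 to 12 to the full-year mix of presenting complaints and discharge diagnoses, so that both runs target the same population. Both variables are already collected.
2. Repeat the check within the discharge-diagnosis strata already planned under Outcome Measures.
3. Count the 3 months from each site's own start. If starts prove to be staggered, add calendar month to the model.
4. Report the shifts from omitting each of the other three quarters as a descriptive benchmark only, with no rule that a larger first-quarter shift indicates a Hawthorne effect.
5. State that residual season and observation effects cannot be separated within one year.

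The cost is a few more model runs and one reweighting step, with no new data. Standardisation deals with change in mix, not with seasonal differences within a complaint or diagnosis, and it will be imprecise for any condition seen mostly in the excluded months. The price is a more cautious reading of the check.
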